### Treatment-Response Prediction Model

The treatment-response prediction model to be validated in study 4 will be developed using data from studies 1 through 3. Candidate predictors will include baseline demographic characteristics (age, sex, and education), clinical variables (baseline symptom severity scores, disorder diagnosis, duration of illness, and medication status), music preference profiles (STOMP-R scores), and baseline neurophysiological features (resting-state EEG spectral power and frontal alpha asymmetry). The outcome variable for model development will be treatment response at 8 weeks, defined as a reduction of 50% or greater in the disorder-specific primary outcome measure. Model development will use logistic regression with regularization (elastic net) to handle the potentially large number of candidate predictors relative to the sample size, with internal validation using 10-fold cross-validation. The final model will be prespecified and locked before its application to the study 4 validation cohort. Model performance in study 4 will be assessed using discrimination metrics (area under the receiver operating characteristic curve, sensitivity, and specificity) and calibration measures (Hosmer–Lemeshow test and calibration plots). Should the cumulative sample from studies 1 through 3 prove insufficient for robust model development, alternative approaches such as penalized regression or decision-tree methods will be considered, and the model validation in study 4 will be framed accordingly. A detailed statistical analysis plan for the prediction model will be finalized before study 4 enrollment commences.

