**Methods:**

This multistage research program is being conducted at Peking Union Medical College Hospital and comprises four sequential studies: (1) a cross-sectional pilot study (n=20) to benchmark clinical and electroencephalography features, (2) a prospective cohort study (n=80) evaluating the efficacy and safety of nonindividualized receptive music therapy, (3) a pilot randomized clinical trial (n=300) comparing nonindividualized therapy with IMT over 8 weeks, and (4) a prospective validation study (n=60) of a treatment-response prediction model. Participants include adults aged 18 to 60 years with mild-to-moderate major depressive disorder, generalized anxiety disorder, or primary insomnia, along with healthy controls. In the nonindividualized arm, participants engage in daily 30-minute listening sessions using therapist-curated instrumental tracks designed to regulate mood. In the IMT arm, an AI generation pipeline creates bespoke instrumental tracks based on weekly participant preferences regarding tempo, instrumentation, and emotional valence. To equalize participant–researcher contact across arms and reduce attention and expectation bias, participants in the nonindividualized arm complete a weekly music-experience questionnaire matched in length and timing to the IMT arm’s weekly preference assessment, and treatment credibility and outcome expectancy are measured at baseline in both arms. The primary outcomes are the response rate at 8 weeks (defined as ≥50% reduction in Montgomery-Åsberg Depression Rating Scale [MADRS], Hamilton Anxiety Rating Scale [HAMA], or Pittsburgh Sleep Quality Index [PSQI] scores) and changes in quantitative electroencephalography characteristics. Secondary outcomes include changes in MADRS, HAMA, and PSQI scores from baseline to 8 weeks.

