## Methods

### Study Design

The program comprises 4 sequential studies (Table 1 and Figure 1): 1 cross-sectional study, 2 prospective cohort studies, and 1 randomized controlled trial (RCT). The target populations are adults with mild-to-moderate major depressive disorder (MDD), generalized anxiety disorder (GAD), or primary insomnia (PI), as well as healthy controls. All studies use a common assessment framework including baseline demographics, clinical characteristics, symptom severity, and electroencephalography (EEG), with follow-up assessments at weeks 1, 2, 4, 6, and 8.

**Table 1. T1:** Study description of the individualized (receptive) music therapy research program.

Study	Description	Translational role
Study 1 (Cross-sectional)	A pilot study (n=20; 5 per group: MDD^a^, GAD^b^, PI^c^, and HC^d^) to characterize clinical features and EEG^e^ patterns across the target disorders and healthy controls. These findings will be benchmarked against prior literature to calibrate study procedures.	Findings will be used to calibrate assessment procedures, verify the feasibility of EEG protocols, and generate preliminary hypotheses regarding disorder-specific neurophysiological signatures to guide the analytical framework of subsequent studies.
Study 2 (Prospective Cohort)	An open-label evaluation (n=80; 20 per group: MDD, GAD, PI, and HC) of the efficacy and safety of 8-week nonindividualized receptive music therapy with concurrent EEG monitoring.	Establishes preliminary efficacy benchmarks and identifies EEG features associated with treatment response. These data serve as the reference standard against which the added benefit of individualization is evaluated in study 3.
Study 3 (Randomized Controlled Trial)	A pilot RCT^f^ (n=300; MDD, GAD, and PI) in which participants are randomized 1:1 to receive either nonindividualized receptive music therapy or IMT^g^ for 8 weeks.	Provides the first direct comparison of individualized versus nonindividualized approaches. Clinical and EEG data from studies 1‐3 are pooled to develop a treatment-response prediction model.

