Study 4 (Prediction Validation)	A prospective cohort study (n=60) in which all participants receive IMT, and the prespecified prediction model derived from studies 1‐3 is applied at baseline to classify participants as predicted responders or nonresponders.	Validates the prediction model in an independent sample. Unlike study 2, which evaluates the nonindividualized intervention, study 4 exclusively administers IMT and focuses on predictive accuracy rather than treatment efficacy.

a MDD: major depressive disorder.

b GAD: generalized anxiety disorder.

c PI: primary insomnia.

d HC: healthy control.

e EEG: electroencephalography.

f RCT: randomized clinical trial.

g IMT: individualized (receptive) music therapy.

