## Discussion

### Principal Findings

This protocol describes a multistage research program designed to develop, evaluate, and optimize an AI-enabled IMT intervention for common mental disorders. We hypothesize that IMT, by tailoring musical stimuli to patient-specific preferences through generative AI, will yield superior response rates compared with nonindividualized receptive music therapy, and that these therapeutic effects will be accompanied by measurable changes in quantitative EEG characteristics. The sequential study design enables iterative refinement: study 1 establishes neurophysiological benchmarks, study 2 provides preliminary efficacy data for the nonindividualized protocol, study 3 directly compares the 2 approaches in an RCT, and study 4 validates a prediction model to identify patients most likely to benefit from IMT.

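### The response model pools two treatments without listing treatment as a predictor, so in the all-IMT study 4 it will under-predict response by about 0.58 of any IMT advantage

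*Protocol article*

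**What the plan says.** The section Treatment-Response Prediction Model sets the source of the training data: "The treatment-response prediction model to be validated in study 4 will be developed using data from studies 1 through 3". Table 1 (study 3 row) says the same of the clinical and EEG data, which "are pooled to develop a treatment-response prediction model". The outcome is response at week 8, meaning that the score on the scale for the participant's own disorder has at least halved. The candidate predictors are demographics, clinical variables, STOMP-R music preferences and baseline EEG features. Treatment received is not among them. The method is elastic-net logistic regression, and the model is fixed before study 4 and then assessed there for both discrimination and calibration.

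The contributing studies differ in treatment:

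- **Study 1:** "a cross-sectional pilot study (n=20) to benchmark clinical and electroencephalography features". No intervention is described.
- **Study 2:** "An open-label evaluation (n=80; 20 per group: MDD, GAD, PI, and HC", all on nonindividualized therapy.
- **Study 3:** "participants are randomized 1:1 to receive either nonindividualized receptive music therapy or IMT".
- **Study 4 (validation, n=60):** a cohort "in which all participants receive IMT, and the prespecified prediction model derived from" the earlier studies is applied at baseline.

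Principal Findings describes the result as a study that "validates a prediction model to identify patients most likely to benefit from IMT", and Future Directions proposes a decision-support tool on that basis. The same section of the article defers a detailed analysis plan for the model to a date before study 4 enrollment.

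**The concern.** A model fitted to two treatments without knowing which one each person received predicts a mixture of the two response rates. Study 4 is not a mixture. If IMT works better, as Principal Findings hypothesises, the mixture rate lies below the rate in study 4. A real treatment advantage then appears as poor calibration of the model. Any cutoff used to label predicted responders is also chosen on the wrong scale, which affects sensitivity and specificity.

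Two related statements do not fit the design. Some records in studies 1 through 3 cannot have the stated outcome at all, so the named training set cannot be the one used. And a cohort in which everyone receives IMT can show who responds under IMT, but not who does better on IMT than on nonindividualized therapy.

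**Working it through.** **Inputs from the article.** Table 1 and Sample Size Calculation give the counts, which reproduce exactly:

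- Study 1: 4 × 5 = 20.
- Study 2: 4 × 20 = 80.
- Study 3: 3 diagnoses × 2 arms × 50 = 300.
- Sample Size Calculation also gives a control response of 70%, differences from 0 to 30 points, and 20 points as the threshold for clinical importance.

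The article gives no size or calibration target for the prediction model, so there is no stated figure to reproduce for it.

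**Records that can carry the outcome**

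| Source | Records | Definable response | Treatment |
|---|---|---|---|
| Study 1 | 20 | 0 | none |
| Study 2 patients | 60 | 60 | nonindividualized |
| Study 2 healthy controls | 20 | 0 | nonindividualized |
| Study 3 control arm | 150 | 150 | nonindividualized |
| Study 3 IMT arm | 150 | 150 | IMT |
| Total | 400 | 360 | 210 nonindividualized, 150 IMT |

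Shares: 210/360 = 58.3% nonindividualized and 150/360 = 41.7% IMT. The records without a definable response are 40/400 = 10%.

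Study Design says that all studies share an assessment framework "with follow-up assessments at weeks 1, 2, 4, 6, and 8", which sits oddly with a cross-sectional study 1. Even with a week 8 visit, study 1 has no treatment to respond to.

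**Average gap without a treatment term.** Logistic regression with an unpenalised intercept makes the mean prediction equal the observed rate in the training data. Let p be the control response and d the IMT-minus-control difference:

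- mean prediction = [210p + 150(p + d)]/360
- true IMT rate = p + d
- gap = (p + d) − mean prediction = (210/360)d = 0.583d

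With p = 70%:

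| d (points) | Mean prediction | True IMT rate | Gap (points) |
|---|---|---|---|
| 0 | 70.0% | 70% | 0 |
| 10 | 74.2% | 80% | 5.8 |
| 20 | 78.3% | 90% | 11.7 |
| 30 | 82.5% | 100% | 17.5 |

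At d = 20 this is 0.783 × 60 = 47 predicted responders against 0.90 × 60 = 54. The gap in points does not depend on p.

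**Would study 4 notice?** The binomial standard error of an observed rate in 60 people is:

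- at 80%: √(0.8 × 0.2/60) = 5.2 points, so a gap of 5.8 is about 1.1 standard errors
- at 90%: √(0.9 × 0.1/60) = 3.9 points, so a gap of 11.7 is about 3 standard errors

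**Check by simulation.** The setting was 360 records, three assumed predictors, unpenalised logistic regression and 600 runs for each value of d.

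| d (points) | Mean gap, no treatment term | Mean gap, treatment term set to IMT |
|---|---|---|
| 0 | 0.05 | −0.11 |
| 10 | 5.88 | 0.18 |
| 20 | 11.83 | 0.04 |

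**Records without an outcome.** If they are dropped, calibration does not change. If they were coded as nonresponse (an assumption; the article does not say so), the mean prediction at d = 0 would be 252/380 = 66.3% with 20 such records and 252/400 = 63.0% with 40, instead of 252/360 = 70%.

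**Nonresponders available at 70% against 90%.** All 360 records: 210 × 0.30 + 150 × 0.10 = 63 + 15 = 78. IMT records only: 15.

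**The case against.** The strongest reply is that the model is not finished. The article says what the candidate predictors will include, which need not be a complete list, and it promises a separate plan. Nothing excludes a treatment term. This stands, and it is why the matter can still be settled cheaply. It does not remove the point: the article states which data are pooled, names the predictors and names the all-IMT validation cohort, and nothing in it corrects the mismatch.

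A reader might infer that the model is bound to be miscalibrated. The documents do not support that. The average gap is proportional to the IMT advantage and is zero at the lower end of the article's own range. The 20-point figure is a threshold for importance, not an expected effect. At +10 points, a cohort of 60 would not reliably show the gap. A uniform shift that keeps the ranking of participants also leaves the area under the ROC curve unchanged.

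A reader might also blame the study 1 and healthy-control records for miscalibration. That does not follow, because records without an outcome drop out of the fit.

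Predictor effects may differ between treatments, and tailoring to preference makes this plausible for STOMP-R. The documents give no figure for it, so no size can be claimed.

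Finally, Table 1 describes study 4 correctly as a test of predictive accuracy. The claim about benefit is confined to the discussion, so that part is a matter of wording.

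**Conclusion.** The point holds in conditional form. Followed as written, the model under-predicts IMT response on average by 0.583 of whatever advantage IMT has over nonindividualized therapy: 0, 5.8, 11.7 and 17.5 points for advantages of 0, 10, 20 and 30. Under the article's own hypothesis that IMT is superior, under-prediction is the expected direction.

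The figures assume that:

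- all 360 records have a week 8 outcome;
- response to nonindividualized therapy is the same in studies 2 and 3;
- study 4 participants resemble the development patients;
- no treatment term is added.

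Separately, naming studies 1 through 3 as the source misdescribes the training set by 40 of 400 records, and the benefit claim in the discussion goes beyond what a single-arm study 4 can show.

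The change is recommended rather than essential. The randomized comparison in study 3 and participant safety are untouched, and the treatment variable is already recorded.

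**What to change.** Before the model is locked, write into the pending model plan:

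1. The development set is study 2 patients plus all study 3 participants (n=360). Study 1 and the healthy controls are not used in this model.
2. Treatment received enters as a forced, unpenalised term, and study 4 predictions are made with treatment set to IMT.
3. A short list of penalised treatment-by-predictor terms, and a model fitted to the 150 IMT records alone, are exploratory sensitivity analyses. At 90% response both rest on about 15 IMT nonresponders and will be unstable.

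In Principal Findings and Future Directions, replace the claim about benefit from IMT with one about likely response under IMT. Any statement on who gains more from IMT than from nonindividualized therapy has to come from the randomized treatment-by-predictor terms in study 3.

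The cost is wording and one extra parameter. No usable record is lost, because the 40 excluded records have no outcome to contribute. Once the model is locked, the same correction would cost study 4 its standing as validation of a prespecified model.

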### Outcome Measures

#### Primary Outcome Measure

Response rate at 8 weeks, defined as ≥50% reduction in MADRS, HAMA, or PSQI scores; change in quantitative EEG characteristics from baseline to week 8. Specific EEG features of interest are detailed in the statistical analysis plan.

#### Secondary Outcome Measure

The secondary outcome is change in MADRS, HAMA, and PSQI scores.

#### Safety Outcome Measure

General side effects were measured by the UKU and FIBSER. Psychotogenic effects were measured with the BPRS consisting of suspiciousness, hallucinations, unusual thought content, and conceptual disorganization. Manic symptoms were assessed using YMRS. C-SSRS was also rated throughout the trial for safety purposes.

### Plan for Statistical Analysis

All statistical analyses will be performed using SPSS Statistics (version 23; IBM Corp), R (version 4.3 or higher; R Foundation for Statistical Computing), and MATLAB (MathWorks) with the EEGLAB toolbox for EEG data processing. All hypothesis tests will be 2-sided, with a significance level of *α*=.05.

#### Descriptive and Baseline Analyses

Continuous variables with approximately normal distributions will be summarized as mean (SD) and compared between groups using independent-samples 2-tailed *t* tests (with Welch correction when variances are unequal); nonnormally distributed continuous variables will be summarized as median (IQR) and compared using the Mann-Whitney *U* test. Categorical variables will be summarized as counts (%) and compared using chi-square tests (continuity-corrected for 2×2 tables) or the Fisher exact test when expected cell counts are below 5. Baseline demographic and clinical characteristics will be compared across groups to assess the adequacy of randomization in study 3, and baseline CEQ scores will be compared between arms.

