### Randomization and Blinding

For the RCT, an independent biostatistician will generate the allocation sequence using SAS software (version 9.4; SAS Institute). Randomization will be managed via a secure, web-based system to ensure allocation concealment. Upon confirmation of eligibility and completion of baseline assessments, the system will release the assignment to a research nurse who is not involved in outcome assessment. Outcome assessors will remain blinded to group assignment throughout the trial. Given the nature of the intervention, complete participant blinding is not feasible, as those in the IMT arm engage in weekly preference assessments and music selection, whereas participants in the nonindividualized arm receive therapist-curated tracks without weekly customization. Beyond the impossibility of participant blinding, we explicitly recognize that the weekly preference assessment and track-rating procedure in the IMT arm constitutes an additional, potentially active, component of participant–researcher interaction and engagement that is not present in a conventional nonindividualized protocol. Any between-arm difference in outcomes could therefore reflect not only the personalization of the musical stimulus itself but also this greater attention, engagement, and sense of agency. To mitigate both expectation bias and this attention and engagement confound, several strategies are used: (1) participants in both arms are informed only that they will receive music therapy, without being told which approach is hypothesized to be superior; (2) all participants complete equivalent contact time and daily listening schedules; specifically, participants in the nonindividualized arm complete a weekly music-experience questionnaire covering their listening experience, mood, and engagement, that is matched to the IMT arm’s weekly preference assessment in length, frequency, mode of administration, and degree of staff contact, so that the 2 arms are equated for attention and procedural engagement and differ only in whether the questionnaire responses are used to regenerate the following week’s music; and (3) primary outcomes are assessed by independent raters who have no knowledge of treatment allocation. In addition, to render expectation effects measurable rather than merely assumed, all participants complete a validated treatment-credibility and outcome-expectancy measure (the Credibility/Expectancy Questionnaire, CEQ) after allocation and before the first session; baseline expectancy scores will be compared between arms and entered as a covariate in prespecified sensitivity analyses of the primary outcomes. To assess the integrity of assessor blinding and to characterize residual participant unblinding, both participants and outcome assessors will be asked to guess the participant’s allocation at week 8, and a blinding index (bang blinding index) will be computed and reported. Unblinding of assessors is permitted only in the event of a medical emergency.

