#### Heterogeneity of Target Disorders, Subgroup Analyses, and Multiple Comparisons

Recognizing that MDD, GAD, and PI differ in symptom profiles and neurobiological mechanisms, the primary analysis of study 3 will pool all 3 disorders to maximize statistical power, with diagnostic group included as a stratification factor in the randomization and as a covariate in all pooled models. Treatment × diagnosis interaction terms will be included in the mixed-effects models to assess whether treatment effects vary by disorder. If significant heterogeneity is detected, disorder-specific results will be reported separately. The analytic hierarchy is specified a priori as follows. The pooled treatment effect (IMT vs nonindividualized therapy), adjusted for diagnosis, is the confirmatory primary contrast. Disorder-specific treatment effects (MDD, GAD, and PI analyzed separately) are prespecified secondary, hypothesis-generating analyses. For each disorder, we will report the response-rate difference and the MMRM-derived between-group difference in symptom change with 95% confidence intervals, regardless of statistical significance, so that the direction and precision of the per-disorder estimates are transparent and can inform the design of a future definitive trial. The treatment × diagnosis interaction will be evaluated primarily as a test of effect-modification rather than as a gatekeeper for reporting; disorder-specific estimates will be presented whether or not the interaction term reaches significance, but will be explicitly labeled exploratory. We acknowledge that this pilot is not powered for confirmatory subgroup inference. With approximately 50 participants per arm per disorder (100 per diagnostic group), each disorder-specific contrast has limited power to detect between-arm differences smaller than a large effect, and the trial is powered for precision of estimation rather than for hypothesis testing within subgroups (see Sample Size Calculation). To avoid over-interpreting unstable subgroup estimates, the disorder-specific analyses will be supplemented by a hierarchical Bayesian model in which disorder-specific treatment effects are treated as exchangeable and shrunk toward the overall pooled effect; this borrows strength across the 3 disorders and yields more stable, less extreme per-disorder estimates than fully separate analyses. Posterior means and 95% credible intervals for each disorder will be reported alongside the frequentist estimates. We will not draw definitive efficacy conclusions for any individual disorder from study 3; rather, the per-disorder estimates will be used to generate hypotheses and to inform stratified sample-size planning for the definitive trial. It should be noted that the music therapy protocol uses the same affective trajectory for participants with MDD and GAD, whereas a distinct biphasic trajectory is used for participants with PI. This difference in trajectory design reflects the distinct clinical objectives for each disorder and will be accounted for in the analysis by including trajectory type as a covariate in sensitivity analyses. Because trajectory type is collinear with the PI-versus-(MDD and GAD) distinction, this covariate adjustment will be reported as a sensitivity analysis complementary to the disorder-stratified analyses above. For the family of disorder-specific secondary contrasts, the false discovery rate will be controlled using the Benjamini–Hochberg procedure, and both adjusted and unadjusted *P* values will be reported.

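### Significance tests of pre-allocation baseline variables cannot show whether the study 3 randomization was adequate

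*Protocol article*

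**What the plan says.** Under Descriptive and Baseline Analyses, the protocol article gives the purpose of the baseline comparison: "Baseline demographic and clinical characteristics will be compared across groups to assess the adequacy of randomization in study 3". The same paragraph says what comparing means. Normally distributed variables are "compared between groups using independent-samples 2-tailed *t* tests (with Welch correction when variances are unequal"), other continuous variables go to the Mann-Whitney test, and categorical variables are "compared using chi-square tests (continuity-corrected for 2×2 tables) or the Fisher exact test when expected cell counts are below 5". Plan for Statistical Analysis sets one threshold: "All hypothesis tests will be 2-sided, with a significance level of" .05.

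The allocation is described in three places:

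- Study Design (Table 1): "participants are randomized 1:1 to receive either nonindividualized receptive music therapy or IMT".
- Randomization and Blinding: an independent biostatistician generates the sequence, a web-based system conceals it, and "Upon confirmation of eligibility and completion of baseline assessments, the system will release the assignment".
- Heterogeneity of Target Disorders, Subgroup Analyses, and Multiple Comparisons: "diagnostic group included as a stratification factor in the randomization".

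The CEQ is timed differently. Randomization and Blinding has it completed "after allocation and before the first session; baseline expectancy scores will be compared between arms".

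**The concern.** Once a concealed sequence has been followed, the null hypothesis for any variable measured before allocation is true by design. A P value below .05 is then a chance result and says nothing about whether the randomization worked. A P value above .05 does not show that the arms are alike on a variable that matters for prognosis. The planned tests cannot do the job the article gives them.

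What is at stake is mainly reporting. A sound trial could be described as having faulty randomization, or a chance P value could prompt adjustment for whichever variable happened to cross .05. The response-rate comparison is the most exposed to that, because Primary Outcome Analysis plans it as a chi-square test, which carries no covariates.

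**Working it through.** The article gives no figure of its own for this point, so there is none to reproduce.

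**Inputs from the article.** Two-sided .05 per test; 1:1 allocation stratified by diagnosis; 50 per arm in each of three diagnoses (Sample Size Calculation), so 3 × 50 = 150 per arm; continuity correction for 2×2 tables. The Benjamini–Hochberg procedures cover the disorder-specific contrasts and the EEG feature families, not the baseline tests.

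**Inputs that are assumptions.**

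- *Number of variables, k.* Not stated. The low end is about 8: age, sex, education, illness duration, MADRS, HAMA, PSQI and CGI-S. Adding IMS, UPPSAQ-70, DSQ, TAS and the four STOMP-R categories gives 16. A few items of medical and psychiatric history bring it to about 20.
- *Flag.* Not stated. Any single P<.05 is taken as a flag.

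**Step 1: independent tests of exact size.** The chance of at least one flag is 1 − 0.95^k.

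| k | 1 − 0.95^k |
|---|---|
| 8 | 34% |
| 12 | 46% |
| 15 | 54% |
| 20 | 64% |

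The expected number of flags is 0.05k: 0.4 for k = 8 and 1.0 for k = 20.

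**Step 2: closer to the planned tests.** Three features lower these figures. Symptom scales are correlated. Continuity-corrected tests have true size below .05. Stratified allocation makes an unstratified test conservative for any variable that differs by diagnosis. The simulation used 300 patients, 50 per arm in each diagnosis, Welch t tests on equally correlated continuous variables, continuity-corrected chi-square tests on independent 50:50 binary variables, and 4,000 runs per scenario. The Monte Carlo standard error is at most √(0.25/4000) = 0.8 percentage points. The last column shifts three scales by 1.5 SD according to diagnosis.

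| Variables (continuous + binary) | Correlation | No diagnosis differences | Three scales differ by diagnosis |
|---|---|---|---|
| 8 (6+2) | 0 | 32% | – |
| 8 (6+2) | 0.3 | 30% | 24% |
| 8 (6+2) | 0.5 | 27% | 22% |
| 12 (9+3) | 0.3 | – | 35% |
| 15 (12+3) | 0.3 | – | 42% |
| 20 (16+4) | 0 | 62% | – |
| 20 (16+4) | 0.3 | 55% | 53% |

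With correlated scales the range is 22% to 55%. A simpler simulation with exact-size tests at correlation 0.5 gives 29%, 36% and 42% for 10, 15 and 20 variables, which lies inside that range.

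**Step 3: what a non-significant result would let through.** The smallest standardized difference that reaches P<.05 is about t × √(2/n per arm).

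- All patients: 1.968 × √(2/150) = 0.23.
- One diagnosis: 1.984 × √(2/50) = 0.40.

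Imbalances below these sizes would be non-significant, whatever their prognostic weight.

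**The case against.** The best defence is that little follows from these tests. The article ties no decision, covariate choice or change of analysis to them. Primary Outcome Analysis already puts baseline scores into the models for continuous outcomes, and the Heterogeneity section makes diagnosis a covariate in all pooled models. The article also commits to a statistical analysis plan finalized before database lock. All of this stands, and it keeps the point minor.

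The size is also open to challenge. A reader might infer from 1 − 0.95^k that a sound randomization has a one-in-three to two-in-three chance of being flagged. That needs about 8 to 21 independent tests of exact size, and the planned tests are neither independent nor all of exact size. The article's wording covers demographic and clinical characteristics. Psychosocial instruments are listed as a separate domain, and music preference is set apart in the prediction-model section, so a narrow reading leaves about 8 variables and 22% to 30% with correlated scales. A reader might also infer a rule that one significant result means failed randomization. The article contains no such rule.

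It can be said, too, that a condensed article may leave multiplicity among baseline tests to the full plan. That is fair, but it does not rescue the tests. A Bonferroni correction would hold the chance of any flag to at most 5% and would still not make a P value informative about a null that is true by design.

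Finally, such tests might expose subverted allocation. The article does not state that aim, and an uncorrected 5% screen over many variables is a poor detector because false alarms are expected. None of these arguments defends the stated purpose.

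**Conclusion.** The point holds as a minor one. The article fixes both the tool (tests at .05) and the purpose (judging randomization), and the tool cannot serve the purpose for variables measured before a concealed allocation.

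The false-flag chance is about 22% to 55%, or 34% to 64% if the tests were independent and of exact size. Both ranges rest on 8 to 20 variables and on any P<.05 counting as a flag, and neither assumption is in the article.

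A reader might go further and conclude that the treatment comparison itself is compromised. The article does not support that: no treatment-effect estimate, error rate or sample size depends on these tests. The criticism also does not extend to the CEQ. It is completed after allocation, so an arm difference there is a real question.

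**What to change.** In Descriptive and Baseline Analyses:

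- Delete the clause that gives adequacy of randomization as the purpose, together with the between-arm tests of pre-allocation variables in study 3.
- Present baseline by arm, and by arm within diagnosis, with means, medians or counts, and standardized differences if wanted.
- Keep the arm comparison of the CEQ as a separate item, noting that it is measured after allocation.

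State also that covariates are fixed in advance whatever imbalance is observed. In Primary Outcome Analysis, apply diagnosis and the baseline disorder-specific score to the response-rate comparison as well as to the continuous outcomes. Because the three scales differ, the score should enter within diagnosis.

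The cost is wording, a column of uninformative P values, and a covariate-adjusted model for the response rate that still reports the risk difference and risk ratio. No data collection changes.
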